#### Condensed session overview

The intervention follows a progressive structure combining individual and group-based sessions. A condensed overview is provided below, while the full session-by-session protocol, including detailed objectives, activities, facilitation procedures, and adaptation options, is provided in Supplementary material 1.Session 1 (Group, 45 min): Introduction to the program, establishment of group trust, vocal and physical warm-up with music, group percussion activities, and a closing group song to foster cohesion and shared participation.Session 2 (Individual, 30–40 min): Initial assessment of rhythmic motor participation, emotional response to music, vocal engagement, and ability to follow musical and verbal cues.Session 3 (Individual, 30–40 min): Initiation of individualized activities based on the initial assessment, including instrumental coordination tasks, breathing and relaxation exercises with music, and vocal rhythm/articulation exercises.Session 4 (Group, 45 min): Group rhythm and coordination activities, simple musical improvisation, and group singing to promote social interaction, participation, and vocal engagement.Sessions 5 and 6 (Individual, 30–40 min each): Progression of task complexity according to individual needs, including bilateral motor tasks, faster or more complex rhythmic patterns, relaxation techniques, and more demanding vocal-rhythmic exercises.Session 7 (Group, 45 min): Reinforcement of previous achievements through instrument practice, guided visualization with music, and reading or vocal engagement activities to support coordination, attention, and emotional wellbeing.Sessions 8 and 9 (Individual, 30–40 min each): Consolidation and refinement of acquired skills through review of individualized motor tasks, relaxation activities, and advanced vocal or rhythmic exercises.Session 10 (Group, 45 min): Integration and closure of the program through group rhythm dynamics, collaborative music creation, feedback, individualized recommendations, and a personally meaningful closing song selected by the participant.

The detailed protocol in Supplementary material 1 includes the specific objectives, activities, facilitation procedures, and adaptation options for each session.

Ten-session structured music-based intervention: session schedule (Table 1).

**Table 1 tab1:** Ten-session structured music-based intervention: session schedule.

Week	Session	Format	Duration	Main components	Objective
1	S1	Group	45 min	Welcome, warm-up with music, group percussion, and group song	Social interaction, trust-building, rhythmic engagement
1	S2	Individual	30–40 min	Rhythmic motor assessment, emotional listening, and singing/vocal rhythm	Motor engagement, emotional response, vocal participation
2	S3	Individual	30–40 min	Instrumental coordination, guided breathing, and rhythmic articulation	Coordination, emotional regulation, vocal participation
2	S4	Group	45 min	Group percussion, improvisation, and group song	Social interaction, rhythmic coordination, vocal participation
3	S5	Individual	30–40 min	Bilateral motor skills, faster tempos, and complex phrases	Fine motor skills, vocal participation
3	S6	Individual	30–40 min	Advanced relaxation and long-phrase singing	Fine motor skills, vocal participation
4	S7	Group	45 min	Instrument practice, visualization, reading, and vocal participation	Coordination, attention, emotional engagement
4	S8	Individual	30–40 min	Intensive motor review and deep relaxation	Motor consolidation
5	S9	Individual	30–40 min	Advanced vocal tasks and recitation/singing	Vocal-rhythmic control and motor consolidation
5	S10	Group	45 min	Group music creation, feedback, and meaningful song	Integration, motivation, emotional closure

### Follow-up

A follow-up interview will be scheduled 3 months after completion of the intervention to explore the maintenance of potential effects, the continued use of music-based strategies at home, and participants’ perceived acceptability, usefulness, and relevance of the intervention in their daily lives.

### Assessment

Assessments will be conducted at three main time points, plus one follow-up:Baseline (week 0): Prior to the start of the program. Includes assessment of motor, cognitive, and quality-of-life domains.Week 5 (post-intervention for the experimental group): Repetition of all measures to evaluate initial changes in the experimental group compared to the waitlist group.Week 10 (after the waitlist group intervention): Comprehensive evaluation of both groups following completion of the intervention.Three-month follow-up: Additional evaluation to explore maintenance of potential effects, including quality of life and daily functioning.

Standardized instruments will be used at all time points to measure motor, cognitive, and quality-of-life outcomes. In addition, participants’ perspectives on acceptability and perceived usefulness will be explored qualitatively during the 3-month follow-up interview, in line with multidomain rehabilitation research (12, 30). When feasible, caregivers or family members will also be invited to provide complementary perspectives on functional changes and everyday impact.

Outcome assessments will be conducted by professionals with a clinical background in neuropsychology or rehabilitation. All assessors will receive standardized training in the administration and scoring of the study measures before participant recruitment to ensure consistency and reliability of data collection.

Standard Protocol Items: Recommendations for Interventional Trials (SPIRIT) schedule of enrollment, interventions, and assessments (Table 2).

**Table 2 tab2:** Standard Protocol Items: Recommendations for Interventional Trials (SPIRIT) schedule of enrollment, interventions, and assessments.

Activity	-t1	Baseline (week 0)	Mid-intervention (week 3)	Post-phase 1 (week 5)	Post-crossover (week 10)	Follow-up (3 months)
Eligibility screening	X					
Informed consent		X				
Randomization		X				
Structured music-based intervention: experimental group		X	X	X		
Structured music-based intervention: control/waitlist group				X	X	
Adherence		X	X	X	X	
Assessment: FMA, Action Research Arm Test (ARAT), and WCST		X		X	X	X
Assessment: Behavior Rating Inventory of Executive Function–Adult Version (BRIEF-A)		X		X	X	X
Assessment: Stroke-Specific Quality of Life Scale (SS-QOL)		X		X	X	X
Adverse event reporting		X	X	X	X	X

X indicates that the corresponding activity, intervention, assessment, or reporting item takes place at that time point.

### Outcomes

#### Primary outcome

##### Fugl-Meyer Assessment (FMA)

The FMA is a stroke-specific, performance-based measure designed to assess motor impairment following stroke. It evaluates motor functioning, balance, sensation, and joint functioning, with particular emphasis on voluntary movement patterns. In this study, the motor domain score (including the upper and lower extremity motor subscales) will be used as the primary outcome variable. The motor domain is composed of ordinal items assessing movement, coordination, and reflex activity. The FMA has demonstrated excellent reliability, validity, and responsiveness in stroke populations and is widely considered one of the gold-standard measures for assessing post-stroke motor function in clinical and research settings (31, 32). It was selected as the primary outcome due to its sensitivity to changes in motor performance and its extensive use in stroke rehabilitation trials, allowing comparison with previous studies. It will constitute the main variable for the primary inferential analysis, while the ARAT will be analyzed as a secondary motor outcome, and executive functioning and quality-of-life measures will be interpreted as exploratory outcomes. Items are scored on a 3-point ordinal scale (0–2) and summed to yield a total motor score ranging from 0 to 100, with higher scores indicating better motor function (31, 32).

#### Secondary motor outcomes

##### Action Research Arm Test (ARAT)

The ARAT is a standardized, task-based observational measure of upper-limb function. It assesses grasp., grip, pinch, and gross movement through 19 items grouped into four subscales reflecting functional hand use. The total ARAT score will be used as the main variable for this measure. The ARAT has demonstrated strong reliability, validity, and responsiveness in stroke populations and is particularly sensitive to functional improvements in upper-limb activity (33).

It was selected to complement the FMA by providing an activity-level assessment of upper-limb function, thereby capturing clinically meaningful changes in functional performance. The total score ranges from 0 to 57, with higher scores indicating better upper-limb functional performance (33).

#### Exploratory outcomes

Executive functioning and stroke-specific quality of life will be examined as exploratory outcomes. This classification reflects the relatively brief duration of the intervention, consisting of 10 sessions over 5 weeks, and acknowledges that measurable changes in executive functioning and quality of life may require longer or more intensive interventions. These outcomes are included to explore potential broader effects of the intervention and to inform the design of future studies.

##### Wisconsin Card Sorting Test (WCST)

The WCST is a neuropsychological measure of executive functioning, particularly cognitive flexibility, set-shifting, and problem-solving ability. It requires participants to match stimulus cards according to changing sorting rules based on feedback, thereby assessing the ability to adapt to shifting task demands (34). Responses are evaluated across multiple indices, including categories completed and errors, with perseverative errors reflecting difficulty in cognitive flexibility. In this study, the number of perseverative errors will be used as an exploratory executive function variable, as it is considered one of the most sensitive indicators of cognitive inflexibility and impaired set-shifting. The WCST has been widely used in neurological populations, including stroke, and demonstrates good validity for assessing frontal lobe-related executive processes (34). It was selected due to its sensitivity to executive dysfunction commonly observed after stroke and its ability to capture changes in cognitive flexibility targeted by the intervention.

Perseverative errors are reported as a raw score, with higher values indicating greater executive dysfunction (34).

##### Behavior Rating Inventory of Executive Function–Adult Version (BRIEF-A)

The BRIEF-A is a standardized questionnaire designed to assess executive functioning in everyday life. It includes both a self-report version and an informant-report version completed by a caregiver or close relative, capturing ecologically valid aspects of executive behavior.

In this study, the Global Executive Composite (GEC) score will be used as an exploratory measure of everyday executive functioning. The GEC is derived from multiple subscales reflecting behavioral regulation and metacognitive processes. Both self-report and informant-report versions will be collected. The self-report version will be considered the main source for exploratory analysis, while the informant-report version will be used as complementary information. In cases of discrepancy between versions, the results will be reported descriptively and interpreted cautiously. The BRIEF-A has demonstrated good reliability and ecological validity in neurological populations. It is particularly useful for capturing executive dysfunction as it manifests in daily life, complementing performance-based measures such as the WCST (35). It was selected to provide an assessment of executive functioning in everyday life, reflecting real-world cognitive difficulties that may not be fully captured by laboratory-based tests. Scores are standardized T-scores (mean = 50, SD = 10), with higher scores indicating greater executive dysfunction (35).

##### Stroke-Specific Quality of Life Scale (SS-QOL)

The SS-QOL is a validated, stroke-specific self-report instrument designed to assess health-related quality of life across multiple domains relevant to stroke survivors. These domains include mobility, self-care, mood, energy, social roles, communication, cognition, and upper extremity function. In this study, the total SS-QOL score will be used as an exploratory measure of stroke-specific quality of life. The scale consists of multiple items rated on a Likert-type scale, with domain scores summed to obtain a total score reflecting the overall quality of life. The SS-QOL has demonstrated good reliability and validity in stroke populations and is widely used in rehabilitation research to assess patient-centered outcomes (36). It was selected due to its comprehensive and stroke-specific nature, allowing evaluation of the broader impact of the intervention on daily functioning, emotional wellbeing, and social participation. The total score ranges from 49 to 245, with higher scores indicating better quality of life (36).

#### Adherence and acceptability outcomes

Adherence, session attendance, and completion of the intervention will be documented descriptively. Participant-reported acceptability will be explored in the 3-month follow-up interview, focusing on perceived usefulness, burden, and relevance of the integrative format for everyday functioning.

When available, caregiver or family member perspectives will also be collected to complement participant-reported outcomes.

#### Safety outcomes

The intervention is considered low risk as it does not involve invasive or pharmacological procedures.

Adverse events will be systematically recorded in each session using a standardized form. Particular attention will be paid to potential adverse effects such as fatigue, frustration, emotional discomfort, or irritability. Adverse events will be reported to the ethics committee, and appropriate procedures will be followed for their management.

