### Study design

This is a prospective, phased, randomized waitlist-controlled intervention study with a parallel-group design, aimed primarily at evaluating the effects of the intervention on motor function. Upper-limb motor function will be assessed as a secondary motor outcome, while executive functioning and stroke-specific quality of life will be examined as exploratory outcomes. Participants will be randomly allocated to either an experimental group or a control/waitlist group.

The study will be implemented in successive recruitment phases. The first phase will be conducted in a single outpatient neurological rehabilitation center in the Community of Madrid, Spain, and subsequent phases will extend recruitment to additional outpatient neurological rehabilitation centers within the Community of Madrid until the required total sample size is achieved.

In the first recruitment phase, approximately 24 participants are expected to be included, with 12 participants allocated to each group. Recruitment will then continue in subsequent phases across additional centers, maintaining the same eligibility criteria, intervention protocol, assessment schedule, randomization procedures, and outcome measures, until the planned sample of 76 participants is reached.

Two groups will undergo the same overall rehabilitation process. Over a total of 5 weeks (two sessions per week), the experimental group will receive their standard rehabilitation care complemented by a program of music-based activities. The control/waitlist group will receive only standard rehabilitation care during the first 5-week intervention period and will subsequently undergo the music-based program after the experimental group has completed it, thereby effectively switching their roles.

This design ensures that all participants benefit from the intervention while allowing temporal comparison between the groups. This structure is consistent with previous studies of similar music-based rehabilitation programs and supports ethical rigor by ensuring that all participants receive a potentially beneficial intervention.

All participants will be assessed at baseline (week 0), after 5 weeks (post-intervention), and again at 10 weeks (after crossover). A 3-month follow-up will be conducted to explore the maintenance of potential effects.

The study has been preregistered in OSF Registries.^1^ This record is reported as an open science preregistration and is not presented as a clinical trial registry.

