Musical parameters, including tempo, rhythmic complexity, movement amplitude, instrument type, and level of facilitator cueing, will be adapted according to participants’ motor capacity, fatigue, comprehension, and emotional response. Tasks will begin at a level that allows successful participation and will progress by increasing rhythmic complexity, tempo, task duration, bilateral involvement, range of movement, memory load, or degree of independence. Task difficulty will be reduced if participants show excessive fatigue, frustration, loss of postural control, inability to follow instructions, or emotional discomfort. Treatment fidelity will be supported through facilitator training, use of the standardized session protocol, and completion of a session checklist documenting attendance, activities delivered, adaptations made, participant engagement, adverse events, and deviations from the protocol.

Session checklists will be reviewed periodically by the research team to monitor adherence to the protocol and identify deviations requiring corrective action.

The intervention consists of a 10-session structured program delivered twice per week over 5 weeks, including 6 individual sessions and 4 group-based sessions.Individual sessions (30–40 min): Focused on evaluation and individualized work on motor engagement, rhythmic participation, and emotional regulation.Group sessions (45 min): Conducted collectively with all participants, focused on social interaction, motor coordination, and emotional support.

These group-based and receptive components are informed by music therapy and music-based rehabilitation approaches commonly used to support emotional regulation, social interaction, and quality of life in rehabilitation populations. Group singing, shared rhythmic activities, and guided listening are consistent with rehabilitation-oriented music-based frameworks that emphasize emotional expression, social engagement, and patient-centered rehabilitation (6, 7).

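### Adverse event recording is tied to music sessions in the text but to fixed time points in Table 2, so pooled by-arm frequencies in the randomised 5 weeks would not be comparable

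*Protocol article*

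**What the plan says.** The protocol article describes adverse event recording in three places.

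- **Safety outcomes:** "Adverse events will be systematically recorded in each session using a standardized form". The section singles out fatigue, frustration, emotional discomfort and irritability, and says events go to the ethics committee.
- **Music-based intervention:** fidelity is supported by "completion of a session checklist documenting attendance, activities delivered, adaptations made, participant engagement, adverse events, and deviations from the protocol". Adverse events sit beside attendance and activities delivered, so the session meant is a music session.
- **Assessment, Table 2:** the row "Adverse event reporting" is marked at weeks 0, 3, 5 and 10 and at 3 months. The footnote reads "X indicates that the corresponding activity, intervention, assessment, or reporting item takes place at that time point". The row is not divided by arm, whereas the two intervention rows are.

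On exposure, "The intervention consists of a 10-session structured program delivered twice per week over 5 weeks, including 6 individual sessions and 4 group-based sessions". For the other arm, "The control/waitlist group will receive only standard rehabilitation care during the first 5-week intervention period" (Study design). The log kept under Standard rehabilitation care applies to both arms but is described as covering therapy type, frequency and duration, not adverse events.

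**The concern.** The first 5 weeks are the only period in which randomised treated and untreated participants can be compared. In that period, both recording methods described in the text operate only where there is a music session. Table 2 adds scheduled reporting for everyone, but no section says what is asked at those points, on which form, or over what period.

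The named events are mostly transient and could occur without the programme. The introduction itself notes a high prevalence of depression and anxiety after stroke. For such events, the number recorded depends partly on how often someone asks. If all records were pooled and tabulated by arm, the programme could appear to cause complaints that were merely observed more often. If only treated participants were summarised, there would be no reference against which to judge the low-risk description. Safety is a named outcome, so its records should be interpretable.

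**Working it through.** **Step 1. Session count, which reproduces the plan's figure.**
Sessions per week × weeks = 2 × 5 = 10. By format, 6 individual + 4 group = 10. The waitlist arm has 0 music sessions in the same 5 weeks.

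**Step 2. Add the Table 2 points to both arms.** The row is not arm-specific, so both arms are credited.

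| Points counted, weeks 0–5 | Experimental | Waitlist |
|---|---|---|
| Music sessions only | 10 | 0 |
| Sessions + weeks 3 and 5 | 10 + 2 = 12 | 0 + 2 = 2 |
| Sessions + weeks 0, 3 and 5 | 10 + 3 = 13 | 0 + 3 = 3 |
| Sessions + week 5 only | 10 + 1 = 11 | 0 + 1 = 1 |

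The last row is a sensitivity count, because Table 2 lists no outcome assessment at week 3. The fair post-baseline count is the second row, 12 against 2.

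**Step 3. What the imbalance could do with no recall.** The documents give no adverse event rate, so this is an assumption with a range. Let r be the chance that a background event is recorded at any one capture point, equal in both arms, independent between points, with each point catching only what is present at the time. Then

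P(at least one recorded event) = 1 − (1 − r)^k, where k is the number of capture points.

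| Assumed r | k = 12 | k = 2 | Ratio |
|---|---|---|---|
| 0.02 | 1 − 0.98^12 = 21.5% | 1 − 0.98^2 = 4.0% | 5.4 |
| 0.05 | 1 − 0.95^12 = 46.0% | 1 − 0.95^2 = 9.8% | 4.7 |
| 0.10 | 1 − 0.90^12 = 71.8% | 1 − 0.90^2 = 19.0% | 3.8 |

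There is no true difference between the arms in any row.

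**Step 4. What it does with complete recall.** Suppose every form asks about the whole time since the last contact and participants recall everything. Divide the 5 weeks into 10 half-weeks, each with event probability p. The experimental records cover all 10, giving 1 − (1 − p)^10. The waitlist records at weeks 3 and 5 cover 6 and 4 half-weeks, giving 1 − (1 − p)^6 × (1 − p)^4 = 1 − (1 − p)^10. The two are identical and the distortion is nil.

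The effect of 12 against 2 points therefore runs from none to several-fold. Where it falls depends on the recall period.

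**The case against.** The strongest reply is that Table 2 already covers the waitlist arm. It schedules adverse event reporting at weeks 0, 3 and 5, does not limit it to one arm although other rows are split, and its footnote says a marked item takes place. This stands: a reader who takes the Safety outcomes sentence alone might infer that the waitlist arm has no adverse event capture in the randomised period, and Table 2 does not support that. The reply has limits. The Adherence row is also unsplit and is marked at weeks 0 and 3, when waitlist participants have no programme to adhere to, so an unsplit row is weak evidence of how collection works in that arm. And crediting every Table 2 point to both arms still leaves 12 against 2.

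Second, no between-arm adverse event analysis is stated. The Statistical analysis section names models for the FMA, ARAT, WCST, BRIEF-A and SS-QOL only. This also stands. A reader might infer that the trial is set to report a biased safety comparison, but the article does not propose one. Closer observation during the activity also has a practical purpose, since task difficulty is adjusted for fatigue, frustration and discomfort.

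Third, elicitation outside sessions and recall periods are details that a condensed article may leave to the full protocol, and the session form and scheduled reporting may be meant as complementary. That is a fair reading, and it keeps this point small. It does not remove the need to align two stated schedules that generate records at different rates by arm.

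Fourth, a waitlist form that looks back over several weeks covers more time than a twice-weekly session form. This is correct, which is why the no-recall figures are one end of a range and not an estimate.

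**Conclusion.** The point holds as a modest one about ascertainment. The text ties adverse event recording to music sessions; Table 2 ties it to fixed time points for all participants; nothing links the two. In the randomised 5 weeks this gives about 12 post-baseline capture points in the experimental arm and about 2 in the waitlist arm, so frequencies pooled over all records could not be compared by arm.

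The size is not determined by the document. The excess is nil with complete recall and roughly four- to five-fold with no recall at assumed per-point rates of 2% to 10%. Those rates, their equality across arms and independence between points are assumptions. The count also takes Table 2 at face value for both arms and takes the session form to mean music sessions, which the checklist supports.

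It would be wrong to conclude that waitlist participants go unmonitored, or that a flawed safety test is planned. The primary analysis is unaffected. The issue is whether the safety records will have a usable reference, and this is a cheap improvement, not a defect in the trial's main inference.

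**What to change.** Reconcile the Safety outcomes section with Table 2 as follows.

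1. State that the same adverse event form, with the same recall period, is completed in both arms at weeks 3, 5 and 10.
2. Base any between-arm safety summary for the randomised period on the week 3 and week 5 records only. The week 10 record falls after the waitlist arm has received the programme and belongs to a separate description.
3. Report events recorded at music sessions separately, as a description of treated exposure, and do not pool them into the by-arm comparison.

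The cost is a short extra form per participant at points Table 2 already marks, with no extra staff. Week 3 has no outcome assessment, but the form can be completed at a routine rehabilitation attendance; at the first centre patients typically attend on weekdays, and later centres would need to confirm a suitable contact. Recruitment had not started at the stated protocol version, so the change can be in place before the first participant.
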